**What is the impact of heat exposure on the physiological responses of farmers?**
**Hypothesis 1**: Increased heat exposure will significantly elevate physiological strain, as measured by heart rate and body temperature.**How does heat exposure influence farmers’ work capacity and farming behaviors?**
**Hypothesis 2**: Higher temperatures will reduce work capacity and alter farming behaviors, including daily activity patterns, sleep quality, duration, and energy expenditure.**What is the relationship between heat exposure, work capacity, health, and farming practices on harvest yields?**
**Hypothesis 3**: Heat exposure will lead to reduced harvest yields by impairing farmers’ work capacity and health.**How do these factors indirectly affect the nutritional status of children under five in farming households?**
**Hypothesis 4**: Reduced work capacity and lower harvest yields due to heat exposure will negatively impact child nutrition.

This study systematically investigates these pathways using wearable sensors, GPS tracking, offering valuable insights into climate-related challenges faced by subsistence farmers and their families.

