## Methods

### Health impact pathways of heat on physiological response, agricultural capacity, harvest yield, and nutritional status of children

The first health impact pathway examines physiological strain due to heat exposure, incorporating temperature, humidity, and the Wet Bulb Globe Temperature (WBGT) index. The WBGT is a standardized composite index that quantifies environmental heat stress by integrating multiple meteorological parameters, including air temperature, relative humidity, and solar radiation. It serves as a physiologically relevant proxy for the subjective perception of heat, capturing the cumulative thermal load experienced by the human body under varying environmental conditions, and is widely employed to assess the potential impact of heat on physical performance and safety. As WBGT levels increase, physical work capacity declines, with significant reductions observed at 27–28°C WBGT [38,41,42].

The second health impact pathway examines the relationship between heat exposure, physiological responses, and work capacity. Prolonged exposure to heat increases cardiovascular strain (above ~26–27°C cardiovascular strain can begin to increase), exacerbates pre-existing health conditions, and heightens the risk of heat-related illnesses, including heat stress, heat stroke, and renal failure. These health effects contribute to reduced work performance, affecting the duration and intensity of agricultural labor. Given that heart rate fluctuations result from both physical exertion and heat stress, careful methodological adjustments will be made to differentiate between these factors (e.g., accounting for cardiac drift in wearable device data).

The third health impact pathway examines how heat affects agricultural work capacity, particularly during peak farming periods such as harvesting. Heat exposure may lead to shortened work shifts, more frequent rest breaks, and reduced overall labor productivity, ultimately impacting both crop yields and harvest quality. This pathway investigates the interplay between heat stress, labor dynamics, and agricultural output, while accounting for variations in socioeconomic conditions, farming techniques, and land use.

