### Study procedures and measurements

Participants will be monitored over a 12-week period each year during the harvest season, which coincides with the rainy season in both the Nouna and Siaya HDSS sites, for a duration of three consecutive years. This repeated seasonal monitoring enables the collection of longitudinal data on heat exposure, work capacity, and agricultural productivity, capturing both seasonal dynamics and interannual variability.

At baseline, field workers will collect socio-demographic information using structured questionnaires implemented via Survey Solutions (https://mysurvey.solutions/en/). The digital platform includes multi-level plausibility checks to enhance data quality. Data will be collected using tablets and uploaded directly to the Survey Solutions server either from the field or HDSS offices. Supervisors will review submissions for completeness and consistency; if discrepancies or missing values are identified, forms will be returned to field workers for verification and correction prior to final approval.

Before the onset of participant monitoring, field workers will measure the perimeter of each farmer’s plot and record the types of crops cultivated. These data will be integrated into remote sensing models to support the estimation of harvest yields and agricultural productivity [31].

Participants aged 18 years and older will be equipped with wearable devices (see Chapter 2.4.1 onwards for further details) that continuously monitor heart rate, physical activity, and sleep patterns throughout the study period. These devices will generate high-resolution data on physiological strain, behavioral activity, and recovery dynamics in response to heat exposure, enabling detailed analysis of the relationship between thermal stress and work capacity. Participants are instructed to wear the devices continuously, with data synchronized via the Fitrockr application (https://www.fitrockr.com/). Due to limited smartphone access among participants, field workers will oversee data synchronization using tablets to ensure regular uploads and minimize data loss.

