#### Harvest yield (health impact pathway 3)

Remote sensing data will be used to estimate harvest yields, based on a previously developed and ground-truth validated model [31,48] in the Nouna HDSS. The remote-sensing based model will be adapted to the Kenyan context as a part of the H2H study. Specifically, Sentinel-2 satellite imagery will be processed for the growing seasons of five key crops. To monitor vegetation health and estimate household-level yields, three monthly vegetation indices will be calculated: the Normalized Difference Vegetation Index (NDVI), the Normalized Difference Red Edge Index (NDRE), and the Normalized Difference Water Index (NDWI). These indices, combined with rainfall data, will serve as input parameters for LASSO (Least Absolute Shrinkage and Selection Operator) regression models. A distinct model will be developed for each crop to generate crop-specific yield estimates. For further details, see [31].

Field boundaries will be mapped using GPS devices (Garmin Etrex 10, Garmin USA), with measurements conducted on two separate occasions per field. Field workers will accompany farmers around each field’s perimeter to ensure accurate boundary delineation. This method will enable precise estimation of household-level agricultural output by crop type, while also geolocating fields for linkage to household data.

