#### Structural equation modeling (SEM) and mediation analysis

To assess both direct and indirect effects of heat exposure, the study will employ Structural Equation Modeling (SEM) with mediation analysis. This approach enables the simultaneous estimation of multiple pathways linking heat exposure to physiological stress, work capacity, harvest yields, and child nutrition, providing a comprehensive understanding of the cascading impacts of heat stress.

Direct effects will be assessed by evaluating the independent influence of heat exposure on physiological stress (e.g. heart rate, energy expenditure), work capacity (e.g. labor duration, frequency of rest breaks), and child nutritional status. These analyses will offer insights into the immediate physiological and occupational impacts of heat and their direct links to health outcomes in children.

Beyond direct effects, SEM will estimate indirect pathways through which heat exposure impacts agricultural productivity and child nutrition. The central hypothesis posits that heat exposure induces physiological stress, which subsequently reduces work capacity, leading to decreased harvest yields and, ultimately, to poorer nutritional outcomes in children. Mediation will be tested using specific pathway models, such as:
Heat exposure → Physiological stress → Reduced work capacityHeat exposure → Reduced work capacity → Lower harvest yields → Poorer child nutrition

To quantify the role of mediating variables, indirect effects (e.g. via work capacity) will be compared with total effects (the overall impact of heat exposure on child nutrition), allowing for estimation of the relative contribution of different pathways.

To ensure the validity and robustness of the SEM, model fit will be assessed using multiple indices, including the Chi-square test, Comparative Fit Index (CFI), Tucker-Lewis Index (TLI), and Root Mean Square Error of Approximation (RMSEA). Through this rigorous analytical framework, the study aims to generate reliable and generalizable evidence on how heat stress affects the livelihoods and health of subsistence farming households.

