#### Harvest yields (health impact pathway 3)

To assess spatial variation in agricultural productivity and its relationship with heat exposure, we will conduct geospatial analyses using Geographic Information System (GIS) tools. Field boundaries – mapped via GPS – will be overlaid with remote sensing data to extract vegetation indices for each field, enabling a spatially explicit assessment of crop health and yield under varying environmental conditions.

Household-level agricultural production will be estimated using LASSO (Least Absolute Shrinkage and Selection Operator) regression models, incorporating variables such as crop type, phenological stages, and time-series vegetation indices – specifically the Normalized Difference Vegetation Index (NDVI), Normalized Difference Red Edge Index (NDRE), and Normalized Difference Water Index (NDWI) – derived from Sentinel-2 satellite imagery, as well as rainfall data from CHIRPS. To improve model robustness and prevent overfitting, five-fold cross-validation will be used to optimize model parameters and assess predictive performance.

Separate LASSO models will be developed for each major crop type, following established methods [31], thereby enhancing model specificity and improving yield forecasts at the field level. This modeling approach allows us to link remote sensing indicators to field-level agricultural output with high spatial and temporal resolution.

To evaluate the influence of heat exposure on productivity, we will identify and compare high- and low-yield regions in relation to spatial and temporal variations in temperature, integrating both indoor and outdoor temperature data. Additionally, fluctuations in temperature, humidity, and extreme weather events will be included in the analysis to assess their contributions to yield variability and to control for potential environmental confounders.

By embedding these geospatial analyses within the broader analytical framework, we aim to generate nuanced insights into how environmental stressors – particularly heat – affect agricultural output at the household level, and how this, in turn, may mediate impacts on work capacity and child nutrition.

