### Harvest outcome

Agricultural yield is strongly influenced by weather-related factors, with rising temperatures and climate variability posing significant threats to food security. Kotir (2011) demonstrated that warming temperatures could substantially reduce major cereal yields in sub-Saharan Africa (SSA) [57]. Serdeczny et al. (2017) projected that SSA will experience increased aridity, extreme heat, and altered rainfall patterns due to climate change, which could exacerbate undernutrition rates [28]. Given that a large segment of the population in Burkina Faso and Kenya depends on rainfed agriculture, these climatic shifts place subsistence farming communities at high risk [28]. As agricultural systems become less predictable, subsistence farmers may struggle to maintain stable harvests, potentially leading to increased rural-to-urban migration and worsening nutritional outcomes, particularly for children [28]. Sultan and Gaetani (2016) emphasized that West Africa’s reliance on rainfed agriculture, coupled with limited adaptive capacity, makes it particularly vulnerable to climate change [21]. Both Burkina Faso and Kenya are experiencing climatic shifts, characterized by rising temperatures, changes in monsoonal rainfall patterns, and more frequent climate extremes [21]. There is compelling evidence that agricultural yields in West Africa are already declining due to increasing temperatures, with variable rainfall and elevated CO2 levels further affecting production [21]. These reductions in harvest yields directly impact subsistence farmers, with cascading effects on nutritional status and food security [21]. Food security and climate resilience are intricately linked to agricultural practices and adaptation strategies. Douxchamps et al. (2015) highlighted that crop diversification, conservation agriculture, agroforestry, livestock integration, improved crop varieties, and fertilizers can enhance farm productivity and food security in West Africa [5]. The study categorized households into four types – subsistence, diversified, extensive, and intensified farming systems – each with different levels of food security and vulnerability [5].

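### Hypothesis 3 can be confounded by heat acting directly on crops, and the satellite yield measure cannot show labour lost once the crop is mature

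*Protocol article*

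**What the plan says.** Hypothesis 3 (Background) reads in part: "Heat exposure will lead to reduced harvest yields by impairing", with farmers' work capacity and health as the mediators. The third health impact pathway in Methods is about "how heat affects agricultural work capacity, particularly during peak farming periods such as harvesting".

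The section on structural equation modelling (SEM) and mediation describes two kinds of effect. For the first, "Direct effects will be assessed by evaluating the independent influence of heat exposure on physiological stress", and the list goes on to work capacity and child nutritional status. Harvest yield is not in it. For the second, "SEM will estimate indirect pathways through which heat exposure impacts agricultural productivity and child nutrition". The one example chain that contains yield runs from heat through reduced work capacity to yield and then to child nutrition. Indirect effects are compared with a total effect, but that total is defined for child nutrition, not for yield.

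Yield is a model prediction. Sentinel-2 imagery from the growing seasons gives three vegetation indices: "These indices, combined with rainfall data, will serve as input parameters for LASSO" (Methods, Harvest yield). Table 1 lists vegetation indices and field boundaries under harvest yield, and lists rainfall under exposure.

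On timing, "Participants will be monitored over a 12-week period each year during the harvest season", and the same sentence says that this season coincides with the rainy season. On mechanism, the Discussion (Harvest outcome) says: "Agricultural yield is strongly influenced by weather-related factors, with rising temperatures and climate variability posing significant threats to food security". It adds that West African yields are already falling because of higher temperatures.

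**The concern.** By the article's own account, heat acts on both the farmer and the crop. Heat is then a common cause of the mediator (work) and the outcome (yield). If the yield equation contains work but not heat, the work coefficient takes up part of the crop damage, and the result reads as lost labour.

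The second difficulty is the outcome. A prediction built from the standing crop and rainfall has no input that changes when a mature crop is gathered late, partly or not at all. Harvest is the labour phase that the third pathway names.

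What is at stake is the central mediation claim. The labour-mediated effect of heat on yield could be overstated through the first fault, while losses of labour at harvest go unseen through the second.

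**Working it through.** **Plan's own figure.** None is given for Hypothesis 3. The only sample-size figure, 63 per group for 5 bpm in heart rate, does not bear on this point. All path coefficients below are assumptions.

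**1. Does other text supply the missing path?**
- Data analysis, Heat (pathway 1): diurnal temperature range, humidity shifts and extreme weather enter the regression and SEM models as covariates or interactions. The heat exposure is not named as a predictor of yield.
- Data analysis, Harvest yields (pathway 3): "fluctuations in temperature, humidity, and extreme weather events will be included in the analysis to assess their contributions to yield variability". This relates temperature to yield but has no work-capacity term, so it cannot separate crop damage from lost labour.
- Methods, end of the pathways section: the external factors named for control are soil fertility, rainfall variability and market fluctuations. Heat acting on the crop is not named.

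None of the three puts heat and work capacity together in a yield equation.

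**2. Size of the bias.** Let heat H and work W be standardised, with W = -aH + error and yield Y = -cH + bW + error. The true mediated effect is -ab. If H is left out of the yield equation, the slope of Y on W is b + ac. The estimated mediated effect is then -a(b + ac), and its ratio to the truth is 1 + ac/b. With b = 0.3:

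| a | c | true -ab | without direct path | ratio |
|---|---|---|---|---|
| 0.2 | 0.15 | -0.060 | -0.066 | 1.10 |
| 0.4 | 0.15 | -0.120 | -0.144 | 1.20 |
| 0.4 | 0.3 | -0.120 | -0.168 | 1.40 |
| 0.6 | 0.5 | -0.180 | -0.360 | 2.00 |

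A simulation of 1,000,000 units per setting agreed to within 0.001. Adding the direct path restored the true value each time. With c = 0 there is no bias.

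**3. No true labour effect (b = 0), n = 210, three-variable model, independent units.** The work-to-yield slope is ac and the mediated effect is -a × ac.
- a = c = 0.5: slope 0.25, mediated effect -0.125, declared significant in 96% of samples.
- a = c = 0.4: slope 0.16, mediated effect -0.064, 64%.
- a = c = 0.3: slope 0.09, mediated effect -0.027, 25 to 26%.

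With the direct path included, the rate was about 5% in each case.

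**4. Would the planned fit checks notice?** Three variables give 3 × 4 / 2 = 6 moments. The model without the direct path has 5 parameters (two paths, the variance of heat and two residual variances), so df = 1. In the step 3 settings, the chi-square test rejected the mis-specified model in 99 to 100% of samples. A significant mediated effect together with an acceptable chi-square occurred in 0% of samples at -0.5 and 0.35% at -0.3.

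**5. Yield seen only as standing crop.** Let the satellite see M = -cH + error, while harvested yield is M + bW. With M as the outcome and the direct path included, the estimated mediated effect was zero (0.001 or less in size) in every setting, against true values of -0.060 to -0.180. Without the direct path, it is the spurious -a²c. At a = 0.4 and c = 0.3 that is -0.16 × 0.3 = -0.048. At a = 0.6 and c = 0.5 it is -0.36 × 0.5 = -0.180, which equals the true value although none of it comes from labour. Correcting the SEM alone is therefore not enough for harvest labour.

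**6. Rainfall.** It is an exposure variable in Table 1 and an input to the yield prediction. Part of any rainfall–yield association is then built in.

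**The case against.** The strongest reply is that an article need not list every path. The SEM is said to cover direct and indirect effects and several pathways at once, the chains are given as examples, a causal diagram is still to be drawn, and the framework figures are not shown here. The Figure 2 caption says that rainfall is considered, so the rainfall paths may already exist. This stands as far as it goes: one can say that no direct heat-to-yield path is named, not that the model has none.

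Four stronger readings are tempting, and the document does not support them.
- *Hypothesis 3 is not identifiable.* The simple model has df = 1 and is over-identified. The fault is bias from an omitted path.
- *Crop damage will be reported as lost labour in 96% of studies.* That figure needs paths of -0.5, and the planned chi-square, CFI, TLI and RMSEA would expose so strong an omission. The article does not say what follows from poor fit. A weaker omission is harder to detect but also biases less.
- *The yield measure misses all labour.* The monitored season is said to coincide with the rainy season, and planting or weeding can alter vegetation indices. Only labour lost after the crop is mature leaves no trace.
- *The Kenyan yield model has no harvest data to be fitted to.* The article says that the model will be adapted and refers elsewhere for detail. Table 1 is not a full data inventory, so silence there proves nothing.

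This is also a feasibility phase, the primary outcome is heart rate, and the Limitations already urge caution about the yield model. That lowers the urgency. It does not remove the point, because the stated direct-effect list, yield measure and monitoring window together fix what Hypothesis 3 can show.

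**Conclusion.** The point holds in a limited form and should be fixed. As described, Hypothesis 3 is open to confounding and only partly measurable. No direct heat-to-yield path is named although the article recognises that heat harms yields, so the work-to-yield slope becomes b + ac instead of b. Over the assumed ranges shown, the mediated effect is overstated by 10% to 100%, and by 40% at middle values. The documents give no coefficients, so the size is illustrative; the direction follows if heat lowers both work and crop growth. Separately, a prediction from growing-season indices and rainfall carries no information on labour lost once the crop is mature. An effect through that labour is estimated as zero when the direct path is included. Labour earlier in the season may still be captured.

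**What to change.** 1. State heat-to-yield, rainfall-to-yield and rainfall-to-work paths in the SEM, and test Hypothesis 3 on the work-to-yield path given heat and rainfall. This costs only wording. In the three-variable case it uses the one degree of freedom (6 parameters for 6 moments), so fit indices no longer test that part. The path should therefore be specified in advance, not added after a poor fit.
2. After harvest, add a few Survey Solutions items on farmer-reported harvested quantity by crop, at least in a subsample. Use this as an outcome for Hypothesis 3 alongside satellite yield. Reports will be noisy, and a contact may have to be scheduled, since the article describes none for this purpose. Without these data, limit the Hypothesis 3 conclusion to labour that affects the standing crop.
3. As a sensitivity analysis, repeat the SEM with a yield prediction that omits rainfall. This departs from the validated model and may predict less well, so it should not replace the main version.

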#### Advanced analytical methods

Given the complex and non-linear interactions between heat exposure, agricultural productivity, and health outcomes, the study will complement traditional statistical approaches with selected applications of artificial intelligence (AI).
Artificial Neural Networks (ANNs) will be applied to integrated datasets that include indoor temperature, heart rate, anthropometric data, and crop yields to model physiological stress and child nutritional status. These models are well-suited to detect non-linear relationships and interactions among diverse inputs and may offer predictive insights that complement regression-based inference.Recurrent Neural Networks (RNNs), particularly Long Short-Term Memory (LSTM) networks, will be used to analyze temporal dynamics in time-series data, including heart rate, ambient and indoor temperatures, and work/rest cycles. These models will help identify lagged effects of heat stress, such as cumulative physiological burden or delayed impacts on productivity and nutritional outcomes.

To ensure robustness and interpretability, all models will be evaluated using cross-validation techniques and compared against traditional statistical benchmarks. Where applicable, we will explore the use of interpretable AI methods (e.g., SHAP) to identify key drivers and support policy-relevant insights.

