A sample size of 63 participants per group is estimated to detect a mean difference of 5 bpm in heart rate with 95% confidence and 80% statistical power. To accommodate potential attrition and inter-individual variability, the H2H study will enroll a total of 210 participants across 25 villages within the HDSS sites during the feasibility phase.

In the Nouna HDSS, the H2H study is nested within a cluster randomized controlled trial (cRCT) evaluating the effectiveness of cool roof coatings as a passive home cooling intervention (DRKS trials registry number DRKS00023207) [46]. Cool roof coatings are designed to reflect solar radiation and exhibit high thermal emittance, thereby reducing indoor temperatures [47].

The cRCT includes 600 households, with 300 households randomly assigned to receive the cool roof intervention and 300 serving as controls. For the H2H study, farmers will be equally sampled from both intervention and control households to ensure balanced exposure conditions. The H2H study does not treat the cool roof intervention as a direct proxy for heat exposure but considers it a potential modifier of recovery following occupational heat stress.

This nested design facilitates the investigation of both direct and indirect heat-related pathways [1]: direct exposure during agricultural work – analyzing physiological responses, work capacity, and productivity; and [2] post-exposure recovery at home, examining whether improved indoor thermal environments enhance recuperation and influence subsequent health and labour outcomes.

While the cool roof cRCT focuses on the effectiveness of home cooling, the H2H study is primarily concerned with occupational heat exposure. Nevertheless, the interaction between workplace heat stress and home-based recovery conditions is a central component in understanding the cumulative effects of heat on health and productivity over time.

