#### Anthropometric measurements (health impact pathway 4)

Anthropometric measurements will be collected from children under five years of age to assess the prevalence of undernutrition in relation to household agricultural production. Interviewers will use tared weighing scales, stadiometers, and length boards (all provided by Seca, Germany) to measure weight, standing height, and recumbent length, respectively. Each measurement will be taken twice by trained interviewers, with discrepancies checked and the mean value used for analysis. Detailed protocols follow those of Mank et al., who conducted anthropometric assessments in the same study region between 2017 and 2019 [30,49]. All measurements will be taken at the beginning of the harvest season, a period typically marked by reduced household food availability and increased food insecurity.

All measurements will be taken at the onset of the harvest season, a time typically characterized by diminished household food availability and heightened food insecurity.

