#### Work capacity and physiological response (health impact pathway 2)

To further quantify the relationship between heat exposure and farmers’ work capacity, we will apply a combination of regression models and machine learning techniques. These approaches complement the broader analytical framework by enabling the detection of both linear and non-linear associations between environmental conditions and physiological responses.

Key heat exposure variables – indoor and outdoor temperature, humidity, and Wet Bulb Globe Temperature (WBGT) – will be modeled against continuous physiological indicators such as heart rate, activity levels, and sleep patterns. Linear mixed-effects models will be used to account for within-subject variability and repeated measures, with random effects specified at the individual level to capture heterogeneity in exposure and response. These models will incorporate covariates such as socioeconomic status and farming intensity to control for confounding.

Model validation will involve standard diagnostic tools including residual and Q – Q plots to assess normality, and Variance Inflation Factor (VIF) analysis to detect multicollinearity. In parallel, cross-validation and residual error analysis will be employed to test model robustness and predictive accuracy. Sensitivity analyses will explore how natural variations in environmental conditions – particularly fluctuations in temperature and humidity – affect the stability and reliability of the modeled outcomes.

To enhance the physiological assessment of energy expenditure and physical effort, we will deploy the Renkforce GP-102 GPS Logger, which includes an integrated pedometer function. These devices will collect location and movement data every 15 minutes, allowing for the estimation of energy expenditure based on distance traveled, travel speed, terrain changes, and rest intervals.

Time spent in agricultural fields will be georeferenced, with GPS data linked to each participant’s unique ID and merged with socio-demographic characteristics, field boundaries, and movement patterns. This enables a comprehensive analysis of how mobility and environmental exposure interact to shape work capacity.

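### Lagged and cumulative heat effects are assigned to an LSTM, which gives predictions but no effect with an interval, and which has few child-nutrition and seasonal-yield outcomes to work with

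*Protocol article*

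**What the plan says.** All references are to the protocol article.

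- **Why lags matter to the study.** Study participants and sample size describes the interplay of workplace heat and recovery at home as central to understanding "the cumulative effects of heat on health and productivity over time".
- **Method named for lags.** Advanced analytical methods applies recurrent networks, in particular LSTM, to "time-series data, including heart rate, ambient and indoor temperatures, and work/rest cycles", and says of them: "These models will help identify lagged effects of heat stress, such as cumulative physiological burden or delayed impacts on productivity and nutritional outcomes". The AI methods are presented as a complement to traditional statistics. Further, "all models will be evaluated using cross-validation techniques and compared against traditional statistical benchmarks", and where applicable "we will explore the use of interpretable AI methods (e.g., SHAP) to identify key drivers".
- **Inferential model for physiology.** The data-analysis section for pathway 2 says "Linear mixed-effects models will be used to account for within-subject variability and repeated measures", with individual-level random effects. It lists indoor and outdoor temperature, humidity and WBGT as exposures and states no lag window. The same section relates morning home-to-plot travel metrics to ambient and night-time temperature, to learn about readiness the next day. It names no model for this.
- **Other inferential models.** The structural equation model, the LASSO yield models, and the chi-square and logistic models for stunting and wasting state no lagged or cumulative heat term.
- **Promised output.** Expected results, Nutritional status, promises effect sizes as exposure-response functions across all links of the chain.
- **Schedule.** Monitoring runs 12 weeks a year for three years (Study procedures and measurements). For children, "All measurements will be taken at the beginning of the harvest season".

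**The concern.** The article does assign a method to lagged and cumulative heat, so this is not a detail simply left for later. The method does not match the output promised. An LSTM returns predictions, and SHAP divides a prediction among its inputs. Neither gives the effect of heat at a given lag, or summed over lags, with a confidence interval. An exposure-response function for cumulative heat needs exactly that.

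There is also a mismatch with the data. The same sentence extends the LSTM's task to delayed effects on nutrition, an outcome measured at the start of each season and not as a series. Dense inputs do not make up for sparse outcomes.

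At stake is whether the cumulative-heat and recovery question ends with an estimate that can be tested and carried into impact models.

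**Working it through.** The plan gives no figure of its own on this point to reproduce. Its sample size of 63 per group does not enter.

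**1. Which model is stated to estimate a lagged effect?**

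| Model in the article | Effect with an interval? | Lag or cumulative term stated? |
|---|---|---|
| LSTM | No | Yes, as its task |
| Linear mixed models | Yes | No |
| Structural equation model | Yes | No |
| LASSO yield models | Predictive | No |
| Logistic models for stunting and wasting | Yes | No |
| Travel metrics against night temperature | No model named | One night |

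No row combines a stated lag with a named inferential model. The nearest, the travel analysis, does not involve heart rate, which is the primary outcome. One of its two metrics, straight-line distance to the plot, is set by geography.

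**2. How many outcomes does each target supply?**

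Inputs: 12 weeks, 3 years, at least 20 GPS days a year and 210 participants, all from the article. Two further inputs are assumptions: anthropometry is repeated each year (inferred from the schedule), and each participant has a separate household with 1 to 2 young children.

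- Wearable days per farmer: 12 × 7 × 3 = 252 at most; for the cohort, 210 × 252 = 52,920.
- GPS days per farmer: 20 × 3 = 60 at least.
- Readings per child: 1 × 3 = 3 at most, fewer for a child who turns five.
- Readings per child after a monitored season: 3 − 1 = 2 at most, because the first start-of-season reading precedes all monitoring.
- Child readings in the cohort: 210 × 3 = 630 (one child each) to 420 × 3 = 1,260 (two each). Of these, 210 × 2 = 420 to 420 × 2 = 840 follow a monitored season.
- Seasonal yield: at most 3 estimates per household (for each crop), taking one growing season per study year.
- Weeks each year without wearable data: 52 − 12 = 40.

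The scarcity therefore applies to nutrition and seasonal yield, not to heart rate, activity, sleep or work/rest cycles.

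**3. What would a same-day-only slope estimate?**

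This is an illustration. The correlation and lag ratio are assumed, not taken from the article. Let the outcome depend on today's heat with effect β₀ and on yesterday's with effect λβ₀. Let daily heat be stationary with day-to-day correlation φ. Then:

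- same-day-only slope = β₀(1 + φλ)
- cumulative effect = β₀(1 + λ)

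| φ | λ | Slope ÷ acute effect | Cumulative ÷ acute | Slope ÷ cumulative |
|---|---|---|---|---|
| 0.6 | 0.5 | 1 + 0.30 = 1.30 | 1.50 | 1.30/1.50 = 0.87 |
| 0.3 | 0.5 | 1 + 0.15 = 1.15 | 1.50 | 1.15/1.50 = 0.77 |
| 0.6 | −0.5 | 1 − 0.30 = 0.70 | 0.50 | 0.70/0.50 = 1.40 |

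For 0 < φ < 1 and λ > 0, the slope overstates the acute effect and understates the cumulative one. With an opposite-sign carry-over, both directions reverse.

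**The case against.** The strongest reply is that this is a condensed article on a feasibility phase, and that lag windows are normally set in a full protocol or analysis plan, neither of which is shown. That is right as far as the mixed models go. A reader might infer that those models are same-day only, but the article does not say so and excludes no lag. Silence there would not be a finding by itself. What remains is that the article did choose a method for lagged effects, and that method cannot give the promised estimate.

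Four further inferences go beyond the text:

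- **That lagged effects are left entirely to the LSTM.** The article says the networks will help and will complement statistics. It plans benchmark comparisons (naming none with a lag), has the night-to-next-day travel analysis, and gives yield and nutrition an inferential path through the structural equation model.
- **That the network has only three child readings to learn from.** Three is a count per child, and a model would pool children. Setting the cohort totals against a parameter count would also mean assuming an architecture, which the article does not fix.
- **That productivity means crop yield.** The article also uses the word for labour output, which GPS and wearables record daily, and its vegetation indices vary within a season.
- **That same-day models must overstate acute and understate total effects.** This needs same-sign carry-over. The article itself expects pacing and rescheduling, so a rebound in activity is possible.

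**Conclusion.** The point holds in a limited form. The LSTM is the only named model given lagged and cumulative heat as a task, and it yields no lag-specific or cumulative effect with an interval. No inferential model is stated to supply one. For child nutrition the sequence model has at most three outcomes per child, at most two of them after a monitored season. For seasonal yield it has at most three per household. This rests on yearly anthropometry, which is inferred.

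Daily physiological and labour outcomes have ample data, so the gap there lies in the choice of model. The factors 1.30 and 0.87 show the possible size of the error if the mixed models were fitted with same-day heat only. They do not predict what this study would find. The change is worth making before analysis begins, but the point does not undermine the design.

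**What to change.** 1. In the pathway 2 mixed models for heart rate, activity and sleep, pre-specify distributed-lag heat terms: same day, preceding night indoors, and the previous 1 to 3 days. Report the cumulative effect for a stated rise in heat, with a 95% interval from the joint covariance of the lag coefficients, as the inferential answer on lagged heat. Carry this estimate into the exposure-response functions.
2. Describe the LSTM as a predictive complement for daily or finer outcomes, including labour productivity, and use the lagged mixed model as its statistical benchmark.
3. Remove child nutrition and seasonal yield from the LSTM's stated aims. Leave them to the structural equation model and, for nutrition, the planned logistic regressions, with exposure defined over the prior season.
4. State whether anthropometry is repeated each year.

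The cost is analysis wording and a few extra parameters per model. Those parameters will be correlated, so individual lag coefficients may be imprecise. No data beyond those planned are needed: indoor sensors and weather stations record every 15 minutes, and the wearables record continuously during monitoring.
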